#### Secondary outcome measures

2.4.2

The PR data obtained at weeks 4, 8, 18, and 24 will be used as the secondary outcome. The PR plus NP, sperm concentration, semen volume, sperm morphology will be measured by the computer assisted sperm analysis system, and both of these indicators are related to the semen quality. BMI, waist-to-hip ratio, body fat percentage at weeks 4, 8, 12, 18 and 24 compared to that baseline are also considered as secondary outcome measures.

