### Study design and settings

2.1

Our study is a 1:1 randomized controlled trial with two parallel groups and will be reported in accordance with the Standards for Reporting Interventions in Clinical Trials of Acupuncture and the SPIRIT 2013 Statement (19, 20). A total of 72 participants will be recruited for this study, with 36 participants assigned to each group. All participants will receive a course of acupuncture treatment after being informed about the study, risks, and benefits, and after signing an informed consent form. The trial flow chart and time point of the assessment are shown in Figure 1 and Table 1.

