#### Sample size consideration

2.2.6

This trial employed a randomized, double-blind, parallel-group design. Sample size calculations were based on the primary efficacy indicators, estimated as the change in PR from baseline at week 12 of treatment. Based on our preclinical pilot study, acupuncture treatment for asthenozoospermia yielded a mean percentage change of 6.6 ± 4.2, while sham acupuncture treatment showed a mean change of 3.2 ± 3.7. With α = 0.025 (one-tailed) and β = 0.1 (90% power), the critical value was estimated as δ = 5% (1/5 of the mean change). With a 1:1 trial-to-control ratio, each group requires 30 participants. Strict quality control during the trial will limit the loss to follow-up rate to 20%, resulting in a total study sample of 72 participants, and finally 36 in the trial group and 36 in the control group.

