#### Lifestyle intervention

2.3.1

Both the acupuncture group and the sham acupuncture group will receive health education upon enrollment, including suggestions from the researchers to maintain a regular diet, engage in appropriate exercise (Participants will choose a suitable form of exercise and persist with it; Participants will be recommended a combination of aerobic and resistance training, ensuring each session lasts at least 30 min and is performed at least twice a week), maintain good sleep habits, and avoid prolonged sitting (participants will be advised to get up and move for 10–20 min after every 1–2 h of sitting, with no single sitting session exceeding 2 h; they will also be suggested to sleep before 23:00 pm daily, minimizing or avoiding staying up late).

In addition, participants will be suggested not to take or use any Chinese herbal preparations (such as Shengjing Capsules, Qilin Pills, Compound Xuanju Capsules, etc.), health supplements (such as Vitamin E, Coenzyme Q10), drugs (such as L-carnitine, aromatase inhibitors, hormonal drugs, metformin, liraglutide, semaglutide, etc.), or any other health supplements, weight-loss teas that may affect semen quality or body weight from the researcher’s assessment. Additionally, participants will also be advised to avoid hot water sitz baths, moxibustion, acupoint embedding, and physiotherapy during the study period.

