#### Data analysis

2.5.2

Statistical analysis will be performed using SPSS (Chicago, IL, USA). For quantitative data (e.g., PR, sperm concentration, semen volume), normality of distribution will be first assessed. For data meeting normality, descriptive statistics will be presented as mean ± standard deviation. Non-parametric rank-sum tests will be used for non-normally distributed data. Count data will be expressed as frequency and percentage [*n* (%)]. For unordered categorical data, chi-square tests will be applied; for ordered categorical data, non-parametric rank-sum tests will be selected. The test level will be set at α = 0.05. *P* < 0.05 indicated statistically significant differences. For repeated measures data, repeated measures analysis of variance (ANOVA) will be performed. If the sphericity test is not satisfied, the results from the Greenhouse–Geisser correction in one-way ANOVA will be used.

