### Quality control

2.6

All relevant personnel will participate will attend specific training about the study objectives, protocol of intervention strategies, and quality control before the study so as to make them understand the protocol and be consistent in the interventions and evaluations during the study process. Before the trial commencement, two TCM practitioners from the selected department will undergo acupuncture technique training. Subsequent interventions will be performed by these two practitioners. The quality control officer will be responsible for establishing the treatment control and quality assurance system for the clinical study. They shall accurately, thoroughly, and meticulously document study case details according to case report form requirements, ensuring content authenticity and reliability before database entry. Upon study completion, paper case report forms will be stored in a locked cabinet. Investigators cannot modify data. All clinical trial results must undergo validation to ensure data reliability and confirm trial conclusions derive from original data. Corresponding data management measures exist throughout clinical trial and data processing phases.

Data collectors will use randomized number codes during data collection. After data collection concludes, the clinical monitor will unblind the primary blind of the randomized case report form, revealing the corresponding A/B codes (without disclosing the specific names of the A/B procedures). Statisticians use A/B codes instead of procedure names during statistical analysis. Following statistical analysis, outcome evaluators assess the efficacy and safety of the A/B procedures. After evaluation, the clinical monitor unmasks the secondary blind layer of the trial case randomization table, revealing whether the A/B intervention was acupuncture or sham acupuncture.

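### BMI, waist-to-hip ratio and body fat are set only against baseline and no between-arm effect is named, so the text permits a before-after reading that cannot separate acupuncture from the advice given to both arms

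*Protocol article*

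**What the plan says.** Section 2.4.2 of the protocol article lists as secondary outcomes "BMI, waist-to-hip ratio, body fat percentage at weeks 4, 8, 12, 18 and 24 compared to that baseline". This is the only place in section 2.4 where an outcome is given a comparator, and the comparator is the man's own baseline. PR is defined by visit, and the other semen measures by how they are obtained.

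Section 2.5.2 (Data analysis) states: "For repeated measures data, repeated measures analysis of variance (ANOVA) will be performed". If sphericity fails, "the results from the Greenhouse–Geisser correction in one-way ANOVA will be used". It also says: "Non-parametric rank-sum tests will be used for non-normally distributed data". It names neither arm as a factor nor the group-by-time interaction as the effect of interest.

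Section 2.3.1 (Lifestyle intervention) says: "Both the acupuncture group and the sham acupuncture group will receive health education upon enrollment". The advice covers diet, exercise, sleep and sitting time.

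Three other places bear on the reading. Section 2.1 says: "Our study is a 1:1 randomized controlled trial with two parallel groups". Section 2.2.6 bases the sample size on a PR variable "estimated as the change in PR from baseline at week 12 of treatment" and sets acupuncture against sham. Section 2.6 says: "Statisticians use A/B codes instead of procedure names during statistical analysis". Table 1 shows the three obesity measures collected at week 0 and at every later visit.

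**The concern.** Advice on diet and exercise acts directly on BMI, waist and body fat. Men in both arms may therefore improve whether or not needling does anything. A test of change from baseline within the acupuncture arm measures advice, time and trial participation together with acupuncture. Only the comparison with sham removes the shared part.

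The outcome definition names baseline as the comparator, and the analysis section does not say which effect is tested. The fallback wording adds to the doubt: taken literally, a one-way repeated measures ANOVA has time as its only factor, which is a within-arm test. An analyst who followed the text word for word could report a before-after result for each arm and read significance in one arm but not the other as evidence for acupuncture. That pattern is not a test of acupuncture, and it can arise often when the two arms change equally.

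**Working it through.** **1. How the protocol uses change from baseline where it gives figures.** The inputs are in section 2.2.6: change in PR of 6.6 (SD 4.2) with acupuncture and 3.2 (SD 3.7) with sham, one-sided α 0.025, power 90%, 30 per arm.

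- Difference: 6.6 − 3.2 = 3.4.
- Pooled SD: √[(4.2² + 3.7²)/2] = 3.958.
- n per arm = 2 × [3.958 × (1.960 + 1.282)/3.4]² ≈ 28.5, so 29. The t-based version gives 29.5, so 30.

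The stated 30 is reproduced as a comparison of changes from baseline *between* arms. For PR, then, change from baseline is a variable on which the arms are compared. No corresponding figure is given for the obesity measures.

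**2. What a within-arm reading would do.** The documents give no effect or SD for BMI, waist-to-hip ratio or body fat, so the following is an assumption shown over a range. Suppose acupuncture has no effect on these measures and both arms share a mean change of d standard deviations of the change score, with n = 30 completers per arm and a paired t-test at two-sided 0.05.

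- Within-arm power p = P(|T| > 2.045), where T is noncentral t with 29 df and noncentrality d√30.
- The arms are independent, so P(significant in acupuncture, not in sham) = p(1 − p).

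Example for d = 0.3: noncentrality 0.3 × √30 = 1.643, p = 0.355, and 0.355 × 0.645 = 0.229.

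| Shared change d | Acupuncture arm significant | Acupuncture significant, sham not |
|---|---|---|
| 0.1 | 8% | 8% |
| 0.2 | 18–19% | 15% |
| 0.3 | 36% | 23% |
| 0.5 | 75% | 19% |
| 0.8 | 99% | 1% |

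A between-arm test of the change rejects in 5% of cases in every row, because the shared change cancels.

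The same formula without a chosen d: for within-arm power of 30%, 50% or 80%, p(1 − p) is 21%, 25% or 16%.

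There are 3 measures × 5 visits = 15 such comparisons. They are correlated, so the rates apply to each comparison and should not be multiplied up.

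**3. The passages side by side.** Section 2.4.2 supplies a baseline comparator. Section 2.5.2 supplies a model without a named contrast and a one-way fallback. Section 2.3.1 supplies a plausible shared cause of change. No sentence says that the change in these three measures is compared between acupuncture and sham.

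**The case against.** The strongest reply is that section 2.4.2 defines a measure and not a test. Change from baseline is an ordinary endpoint, and the sentence claims nothing for acupuncture. The trial is randomized, parallel and sham-controlled; the PR sample size compares changes between arms; and the statisticians work by coded arm. A rank-sum test is most naturally a two-group test, and no paired t-test or signed-rank test appears in the plan. The shared advice is balanced by randomization and cancels once the arms are compared. The choice of model term is often left to an analysis plan, which is not shown here, and section 2.5.2 is equally silent about PR.

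Most of this stands. A reader might infer that the randomized comparison will not be used for the obesity outcomes, or that a significant change will be credited to acupuncture with no between-arm test. The documents do not support either inference: nowhere do they say that only within-arm tests will be done, and the planned methods can supply the arm comparison.

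The reply does not remove the ambiguity. For these three outcomes the article goes beyond silence and names baseline as the comparator. The between-arm use of change is shown for PR only. Coding the arms keeps them separate and masked but does not say which effect is tested.

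**Conclusion.** The point holds as a minor clarification on secondary outcomes. The text leaves the randomized contrast for BMI, waist-to-hip ratio and body fat unstated, and its literal wording permits a before-after test that cannot separate acupuncture from advice given to everyone.

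The size is conditional. It would matter only if within-arm tests were used, and the tabulated rates rest on assumed shared changes, on 30 completers per arm and on a true null effect of acupuncture on these measures. They illustrate the risk in the wording and are not error rates of this trial. The primary outcome and the sample size are not affected by this point.

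**What to change.** Add one sentence to section 2.4.2 and one to section 2.5.2. They should say that BMI, waist-to-hip ratio and body fat percentage are each compared between acupuncture and sham at each visit, adjusted for the week-0 value (for example by ANCOVA or a baseline-adjusted repeated measures model), with a 95% CI, and that within-arm changes from baseline are descriptive. The reference to a one-way ANOVA should be reworded to match.

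The week-0 values are already scheduled in Table 1, so no new data, visits or participants are needed. Even if a between-arm comparison was intended all along, baseline adjustment is a free gain in precision. Naming week 12 as the main time point for these outcomes, or barring within-arm P values altogether, would be a matter of preference and is not required to settle this point.

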#### Safety evaluation and adverse events

2.4.3

From previous published clinical studies, potential adverse effects of acupuncture may encompass discomfort, queasiness, emesis, heart palpitations, lightheadedness, cephalalgia, reduced appetite, localized bruising, and infections (27). Furthermore, incidents such as needle fracture, retained needles, or syncopal episodes could arise throughout the therapeutic process. All such unfavorable responses and occurrences will be systematically recorded by the assessing personnel.

### Data management and analysis

2.5

#### Data management

2.5.1

The contents of the case report form will be accurately recorded in compliance with the case report form completion guidelines to ensure authenticity and reliability, and subsequently entered into the electronic database. Upon study completion, the paper type of the case report forms will be stored in locked cabinets. And the electronic database will be secured with write-protection to prevent data modification. Eight years after the end of the project, all paper documents need to be shredded, and electronic data need to be deleted.

#### Data analysis

2.5.2

Statistical analysis will be performed using SPSS (Chicago, IL, USA). For quantitative data (e.g., PR, sperm concentration, semen volume), normality of distribution will be first assessed. For data meeting normality, descriptive statistics will be presented as mean ± standard deviation. Non-parametric rank-sum tests will be used for non-normally distributed data. Count data will be expressed as frequency and percentage [*n* (%)]. For unordered categorical data, chi-square tests will be applied; for ordered categorical data, non-parametric rank-sum tests will be selected. The test level will be set at α = 0.05. *P* < 0.05 indicated statistically significant differences. For repeated measures data, repeated measures analysis of variance (ANOVA) will be performed. If the sphericity test is not satisfied, the results from the Greenhouse–Geisser correction in one-way ANOVA will be used.

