**FIGURE 1 F1:**
[figure not shown]
Study flowchart.

**TABLE 1 T1:** A process chart of the trial.

Timepoint	Enrollment	Allocation	Treatment phase			Follow-up phase	
	Week-1	Week 0	Week 4	Week 8	Week 12	Week 18	Week 24

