#### Primary outcome measure

2.4.1

Progressive sperm motility (PR) refers to the proportion of sperm in semen that can move in a straight line or with a larger radius, which is an important indicator for assessing sperm motility. We will assess the PR at week 12 as the primary outcome.

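### The outcome and sample size rest on PR at week 12, but the only parametric group comparison named that fits PR is repeated-measures ANOVA, which does not test that difference

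*Protocol article*

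**What the plan says.** Section 2.4.1 (Primary outcome measure) fixes a single visit: "We will assess the PR at week 12 as the primary outcome". Section 2.2.6 (Sample size consideration) sizes the trial on the same visit, with the primary indicator "estimated as the change in PR from baseline at week 12 of treatment". Section 2.4.2 makes the other visits secondary: "The PR data obtained at weeks 4, 8, 18, and 24 will be used as the secondary outcome". Table 1 schedules PR at six time points, from week 0 to week 24.

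Section 2.5.2 (Data analysis) lists PR among the quantitative variables and has normality checked first. For normal data it gives only a descriptive summary (mean and standard deviation). For the rest: "Non-parametric rank-sum tests will be used for non-normally distributed data". Then: "For repeated measures data, repeated measures analysis of variance (ANOVA) will be performed". And: "If the sphericity test is not satisfied, the results from the Greenhouse–Geisser correction in one-way ANOVA will be used". No t-test, ANCOVA, mixed model or week-12 contrast is named.

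**The concern.** PR is measured repeatedly, so repeated-measures ANOVA is the one parametric between-group method in the section that can apply to it. Its standard tests are group, time and group-by-time. The group term compares the arms on the mean over the visits entered. If these include baseline and follow-up, it mixes week 12 with a visit where no effect can exist and with visits the protocol calls secondary. The group-by-time term asks whether the difference between arms varies over visits in any way. Neither estimates the quantity used for sizing, so a positive or negative result need not say anything about week 12.

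Three further features add to this. The classical procedure works on men with a complete set of visits, so by default a man with a week-12 sample but no week-24 sample drops out. The sphericity sentence refers to one-way ANOVA, although the design is group by time. And the choice between a parametric and a rank-sum comparison depends on a normality check of the trial's own data, so the primary test is not fixed in advance.

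**Working it through.** **Inputs from section 2.2.6.** Mean change 6.6 (SD 4.2) with acupuncture and 3.2 (SD 3.7) with sham; one-sided α 0.025; 90% power; 30 per group, raised to 36 for 20% loss.

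**Reproducing the plan's figure.** Difference 6.6 − 3.2 = 3.4. Pooled SD = √((4.2² + 3.7²)/2) = 3.958. The normal approximation for two means gives 29 per group and the noncentral t gives 30 (power 90.5% at 30, 89.5% at 29). The stated 30 is therefore the size for a two-group comparison of change at week 12, a test the analysis section does not name for normal data. After 20% loss, 36 × 0.8 = 28.8, so 29 per group is used below, with two-sided α 0.05.

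**Assumptions not in the protocol.** Six visits enter the ANOVA. Compound symmetry holds, with correlation ρ from 0.3 to 0.8. The per-visit SD is s = 3.958/√(2(1 − ρ)), so that the SD of change stays 3.958. The effect rises linearly to 3.4 at week 12 and then follows one of two paths:

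- Sustained: 0, 1.13, 2.27, 3.4, 3.4, 3.4; mean 2.27.
- Decaying: 0, 1.13, 2.27, 3.4, 1.7, 0.85; mean 1.56.

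**Group term.** This is a t-test on each man's six-visit mean, with SD s√((1 + 5ρ)/6).

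**Group-by-time term.** Noncentrality λ = (n/2) Σ(δₜ − δ̄)² / (s²(1 − ρ)). The denominator is 3.958²/2 = 7.83 for every ρ. Sustained: 14.5 × 10.28/7.83 = 19.0. Decaying: 14.5 × 7.02/7.83 = 13.0. The F test has 5 and 280 degrees of freedom.

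**ANCOVA at week 12.** Effect 3.4, residual SD s√(1 − ρ²), 55 degrees of freedom.

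| Test (29 per group) | ρ = 0.3 | ρ = 0.5 | ρ = 0.8 |
|---|---|---|---|
| Group term, sustained | 97.5% | 80% | 32% |
| Group term, decaying | 77% | 49% | 17% |
| Group-by-time, sustained | 94% | 94% | 94% |
| Group-by-time, decaying | 80% | 80% | 80% |
| Week-12 change, t-test | 89.5% | 89.5% | 89.5% |
| Week-12 ANCOVA | 98% | 96% | 92% |

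**Significance without a week-12 effect.** Set the effect to zero through week 12 and to 3.4 at weeks 18 and 24. In simulation with 30 per arm (3,000 runs per scenario, ρ 0.3 to 0.7), group-by-time was significant in about 99% of runs and the week-12 change test in about 5%.

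**Missing visits.** Take 20% loss plus an assumed 2% or 5% of samples missed at each of the five post-baseline visits. Complete cases per group are 36 × 0.8 × 0.98⁵ = 26.0 or 36 × 0.8 × 0.95⁵ = 22.3. Men with a week-12 value number 36 × 0.8 × 0.98 = 28.2 or 36 × 0.8 × 0.95 = 27.4. Power of the week-12 change test is 85.9% at 26 and 79.5% at 22, against 88.4% at 28 and 87.2% at 27.

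**The case against.** The protocol never says that repeated-measures ANOVA is the primary test or that it runs over all six visits. A fair reading is that it serves the serial secondary data, with the parametric test for week 12 simply left unnamed. An article may leave such detail to an analysis plan that is not shown. This stands as a limit: the visits entered and the primary role are inferences. It does not remove the point. The section states a method, and that method does not match the stated outcome and sizing. The sphericity clause also has meaning only with three or more visits, which rules out a baseline-and-week-12 version in which group-by-time would equal the change-score test.

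Three stronger readings are tempting, and the protocol does not support them.

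- A reader might infer that power collapses. That follows only from looking at the group term at high correlation. Group-by-time, the usual test of differential change, keeps 94% or 80%, and at ρ = 0.3 with a sustained effect the group term exceeds the week-12 test.
- A reader might infer that the fallback does not compare the arms, since a one-way within-subject ANOVA has no group term. The wording is most plausibly a slip for univariate: Greenhouse–Geisser belongs to a repeated-measures model, and the corrected group-by-time test does compare the arms.
- A reader might infer that the plan orders men with a missing visit to be dropped. No such rule is stated. It is the default of the classical procedure, and an analysis plan could provide otherwise.

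The normality check is conventional, and its harm is not quantified here.

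**Conclusion.** The point holds as a mismatch between the named method and the stated primary question. The 30 per group reproduces only as a week-12 two-group comparison, while neither between-group test of the repeated-measures ANOVA is that comparison. The firmest consequence is interpretive: significance can arise entirely from visits the protocol calls secondary. The effect on power depends on which term is read and on trajectories and correlations that the protocol does not give, so no single loss can be stated. The complete-case loss depends on assumed miss rates and is small at the milder end. Within the assumptions used, a baseline-adjusted week-12 test is at least as powerful as every alternative shown, and it answers the stated question.

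**What to change.** Name one primary test in section 2.5.2: the group difference in PR at week 12, adjusted for baseline PR. Either of two forms will do:

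- ANCOVA at week 12; or
- a mixed model for repeated measures on post-baseline visits, with group, visit, group-by-visit and baseline PR, and the week-12 group contrast as the primary result.

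Use all randomised men with available data. Keep any repeated-measures ANOVA for secondary description of the time course, and correct one-way ANOVA there to the univariate repeated-measures test with Greenhouse–Geisser correction. Make the rank-sum test a sensitivity analysis, not a replacement triggered by a normality pre-test.

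The cost is protocol and analysis-plan wording and slightly more analysis work. Both models can be fitted in SPSS, the software already named. The change should be made before unblinding.
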